## Abstract

**Background:**

About 2.4% of Kenyan people (approximately 1.3 million people) are living with HIV. Despite advances in antiretroviral therapy, men continue to experience disproportionately poor engagement in HIV care due to entrenched masculine norms, stigma, and lack of tailored interventions. Mobile health (mHealth) platforms offer a promising strategy to improve care engagement, but evidence on its implementation and impact among men living with HIV is limited.

**Objective:**

This study aims to assess the implementation and potential effects of the Nishauri mHealth intervention on HIV care and treatment outcomes among men in Western Kenya. Specifically, it seeks to (1) analyze its effects on HIV care engagement and treatment outcomes, (2) explore the role of masculine identity in modifying acceptability and uptake, and (3) identify barriers and facilitators of adoption, use, and sustainment.

**Methods:**

We will use a mixed methods design combining a stepped-wedge cluster approach and a pre- and postimplementation assessment across 4 health facilities in Homa Bay County, Kenya. Approximately 347 men receiving HIV treatment who own a smartphone will be enrolled. The stepped-wedge design will sequentially introduce the intervention across the 4 facilities in 2-month intervals following baseline assessments, allowing each site to serve as its own control. Surveys will collect data on sociodemographics, masculinity, intervention acceptability and uptake, and HIV clinical outcomes using validated measures. Intervention effects on pre- and postbinary outcomes will be assessed using the McNemar test, while generalized estimating equations (*α*=.05; *β*=.2; 95% CI) will account for clustering and repeated measures in the stepped-wedge analysis. Focus group discussions (n=5-6) will be conducted with men living with HIV, health care providers, and app developers to explore barriers and facilitators of implementation and adoption. Focus group discussions will be audio-recorded, transcribed, coded, and analyzed thematically.

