### Stepped-Wedge Intervention Approach

#### Strategy

A stepped-wedge design was chosen to allow all facilities to receive the intervention, accommodate phased training and app deployment, minimize contamination between sites, and enable within-facility comparisons over time while controlling for secular trends. The 4 CCCs will undergo a standardized readiness assessment, and phased implementation of the intervention will proceed in sequence according to facility readiness, with sites transitioning from standard care to the mHealth intervention arm over an 8-month period. The phased rollout will occur at 2-month intervals across the 4 participating facilities, resulting in 5 study periods (1 baseline and 4 intervention steps) over approximately 8 months. The 2-month interval was selected to align with routine HIV clinic visit schedules in Kenya [18], allow sufficient time for provider training and participant onboarding, and permit stabilization of app engagement before subsequent facility transitions. This interval is consistent with stepped-wedge evaluations of health service and digital interventions [42] and supports the detection of short-term changes in missed clinic visits and adherence behaviors while accounting for secular trends.

We acknowledge that the 2-month step length is relatively short and may limit detection of longer-term intervention effects within each wedge; however, this interval was selected for programmatic feasibility and alignment with routine HIV care cycles, and outcome measures were therefore chosen to capture proximal, short-term indicators of engagement and retention.

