#### Outcomes

The primary clinical outcome will be missed clinic appointments, while secondary outcomes will include ART adherence (30-day percent visual analog), pharmacy refill consistency (medication possession ratio), and VLS—plasma HIV RNA <200 copies per milliliter. CCC data will be retrieved from facility electronic medical records and patient files, focusing on routinely collected HIV care indicators.

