### Pre- and Postassessment of Implementation Outcomes

#### Participants and Recruitment

The primary study population will comprise men who initiated HIV care and treatment in 2016 or later, following the updated national HIV treatment guidelines. Eligible participants must be between 18 and 55 years of age, own a smartphone or tablet, and be able and willing to provide written informed consent (Multimedia Appendix 1). Men with severe comorbidities or chronic coinfections (eg, cancer or hypertension) that may affect the adoption or use of mHealth interventions will be excluded. Only men who are primarily enrolled at 1 of the 4 participating facilities during the study period will be included. Participant recruitment in each CCC will proceed according to probability proportional to size sampling until the required sample size of 347 participants is reached. Recruitment will occur during routine clinic visits in each facility before the stepped-wedge rollout of Nishauri. Trained study staff or peer educators will introduce the study to clients, provide study information, and collect contact information from those expressing interest. Screening for eligibility will take place in private, either in a clinic or at a location convenient and confidential for the participant. Those who are eligible and interested will then undergo written informed consent.

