#### Quantitative Data Collection and Storage

Quantitative data will be collected at baseline, at 8-month follow-up, and via the Nishauri app data. At baseline, potential participants will be screened for eligibility. Eligible participants will provide written informed consent and locator information before undergoing a short baseline survey lasting approximately 40 minutes. The survey includes validated and pilot-tested modules on sociodemographics, technology acceptance, HIV-related stigma, health literacy, masculinity norms, the System Usability Scale, and intervention acceptability. The survey will be administered electronically using tablets with the REDCap (Research Electronic Data Capture) platform, hosted by the San Francisco Coordinating Center. Data will be collected by trained research assistants (RAs), who were locally recruited and had prior experience in health or social science research. RAs have backgrounds in public health or related disciplines; are fluent in English, Kiswahili, and Dholuo; and will receive study-specific training on the study protocol, ethical conduct of research, informed consent, and standardized data collection procedures prior to data collection. RAs will perform daily quality checks on all forms to identify and resolve errors prior to secure upload to REDCap servers. These servers are firewall-protected, regularly backed up, and housed in a secure environment.

Throughout implementation at each site, app-based metrics will be assessed to capture implementation outcomes related to acceptability and uptake of the Nishauri intervention. Facility-based data will be collected, including who gets the intervention, the date of training, and the date of app installation. App analytics will be used to capture patterns of engagement and uptake among participants. This includes the number of log-ins per user, frequency of use over time, cumulative duration of app sessions, and responsiveness to reminders and notifications (whether SMS or in-app prompts were opened or acted upon). Aggregate metrics such as average log-ins per month, median engagement time, and drop-off points will be analyzed to assess acceptability and sustained use across the study period.

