## Discussion

### Principal Findings

This study is guided by a conceptual framework integrating Proctor’s implementation outcomes framework, TAM, and the masculinity model (Figure 3). It is designed to generate evidence on the implementation and impact of the Nishauri mHealth intervention on HIV care and treatment among men living with HIV in Homa Bay County, Kenya. With this model guiding data collection and analysis, we anticipate findings that will address critical gaps in understanding how mHealth tools perform in resource-constrained, gendered contexts.

By identifying both individual- and system-level factors that influence the adoption, use, and sustainment of the Nishauri platform, this study will generate valuable insights into the dynamic interplay between client- and organizational-level implementation outcomes. Barriers such as limited digital literacy, stigma, poor network coverage, and workflow integration challenges, as well as facilitators like ease of use, perceived usefulness, provider support, and trust in the health system, will be explored in depth. These findings will inform the development of gender-responsive, culturally grounded adaptations to Nishauri as well as other digital health strategies aimed at improving long-term health outcomes for men living with HIV in Kenya and advancing national efforts to close gender gaps in HIV care.

We hypothesize that there will be measurable improvements in HIV service outcomes, particularly ART adherence and clinic retention, among men exposed to the intervention, compared to control periods within the stepped-wedge design. These outcomes will be interpreted in light of confounding variables, such as age, education, and stigma, and supported by app analytics and chart review data. Furthermore, the client outcome of VLS will offer a critical downstream indicator of the intervention’s potential clinical impact.

This study will contribute critical insights into how masculine norms shape the implementation and impact of digital health tools for HIV care. By unpacking how behavioral constructs such as autonomy, stoicism, and fear of vulnerability influence engagement with mHealth interventions, the findings will inform the development of more gender-responsive and contextually grounded digital strategies. These insights have the potential to guide national policies and programs aiming to close gender gaps in HIV care by tailoring interventions to the unique needs and experiences of men.

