### Limitations

While this study uses a stepped-wedge cluster randomized design, several limitations should be noted. First, the number of clusters (health facilities) is small, which may limit statistical power and the ability to control for facility-level confounding. The small number of clusters limits the precision with which facility-level confounders can be modeled and reduces degrees of freedom for estimating random effects. As a result, adjustment for cluster-level confounding is restricted to a limited set of prespecified facility characteristics (eg, size and urban-rural setting), and residual confounding at the facility level cannot be entirely ruled out. To mitigate this limitation, analyses will include fixed effects for time, intention-to-treat estimation, and triangulation with qualitative data to support interpretation of observed effects. Second, reliance on self-reported survey measures for some implementation outcomes (eg, acceptability and adherence) and masculinity factors may introduce recall or social desirability bias. Third, inclusion criteria requiring smartphone or tablet ownership may exclude more men from resource-limited countries, potentially limiting the generalizability of findings. Finally, variations in how the intervention is implemented across facilities—due to staffing, infrastructure, or engagement differences—may influence observed effects. Despite these limitations, the study’s mixed methods approach and triangulation of data sources will enhance the robustness and contextual relevance of the findings.

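### McNemar on two survey waves, one all unexposed and one all exposed, is labelled a test of intervention effects but cannot separate the app from time

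*Protocol article*

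**What the plan says.** The abstract's Methods paragraph assigns the pre-post component its own effect test: "Intervention effects on pre- and postbinary outcomes will be assessed using the McNemar test". It names a different model, one that handles clustering and repeated measures, for the stepped wedge.

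Three places in the body fix the timing of the surveys relative to exposure:

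- Participants and Recruitment: "Recruitment will occur during routine clinic visits in each facility before the stepped-wedge rollout of Nishauri".
- Quantitative Data Collection and Storage: "Quantitative data will be collected at baseline, at 8-month follow-up, and via the Nishauri app data".
- Strategy: the rollout proceeds in 2-month steps over the four facilities, "resulting in 5 study periods (1 baseline and 4 intervention steps) over approximately 8 months".

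On adherence, the article points in two directions. The Outcomes section under the stepped-wedge heading says that "secondary outcomes will include ART adherence (30-day percent visual analog" scale is among them, and then names the source: "CCC data will be retrieved from facility electronic medical records and patient files, focusing on routinely collected HIV care indicators". The Limitations section instead refers to "reliance on self-reported survey measures for some implementation outcomes (eg, acceptability and adherence" as a source of bias, and the abstract says that the surveys collect HIV clinical outcomes. The list of survey modules under Quantitative Data Collection and Storage does not mention adherence.

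**The concern.** The Strategy section gives control of secular trends as one reason for choosing a stepped wedge, and the Stepped-Wedge Analysis section puts a fixed period effect in the model for that purpose. The McNemar comparison discards this protection. It compares one time when nobody has the app with a later time when every facility does, and there is no concurrent control.

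Three things are left out:

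- **Secular trend.** A general change over 8 months, or a change caused by being interviewed a second time, counts as an app effect.
- **Facility.** Pairing within men removes stable differences between facilities. It does not allow for men at the same facility changing together.
- **Length of exposure.** With four facilities crossing over at 2-month intervals, the first and last sites are 3 × 2 = 6 months apart in exposure at a common follow-up date.

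The adherence conflict raises a related problem. If the visual-analogue score exists only in the surveys, it too has just two time points, and the period-adjusted model planned for it has nothing from which to estimate an effect.

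**Working it through.** **Plan's own figure.** The pre-post power section takes 347 men with 10% attrition: 347 × 0.90 = 312.3, which reproduces the stated effective size of about 312. The Results section reports 307 recruited; the same attrition leaves 307 × 0.90 = 276.3. The article gives no sample size or power for the McNemar comparison itself.

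**Step 1: can the surveys identify an effect?** Write the linear predictor as facility effects + time effects + exposure.

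| Data | Rows | Parameters | Rank |
|---|---|---|---|
| Two survey waves, 4 facilities | 8 | 4 facility + 1 time + 1 exposure = 6 | 5 |
| Five periods, staggered crossover | 20 | 4 facility + 4 time + 1 exposure = 9 | 9 |

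With two waves, the time column and the exposure column are identical (0 at baseline and 1 at month 8 in every facility). The effect is not identifiable by this model, whatever test is used. With five staggered periods it is. This assumes survey waves on common dates.

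**Step 2: how often would McNemar mislead?** Suppose the app does nothing and the rate moves from p0 to p1 = p0 − d for other reasons. With within-person correlation ρ:

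- both-wave probability p11 = p0·p1 + ρ·√[p0(1−p0)·p1(1−p1)]
- discordant probabilities b = p0 − p11 and c = p1 − p11
- statistic (B − C)²/(B + C), where B and C are the discordant counts, compared with 3.84 (two-sided 0.05)

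Assumptions that the article does not supply for these outcomes: p0 = 0.20 (borrowed from its missed-appointment power calculation), d from 0 to 5 points, ρ from 0.2 to 0.6, and the two-sided 0.05 level (stated for the stepped-wedge analysis).

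Worked case: n = 312, d = 0.03, ρ = 0.4.

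- p11 = 0.20 × 0.17 + 0.4 × √(0.16 × 0.1411) = 0.034 + 0.0601 = 0.0941
- b = 0.1059 and c = 0.0759, so the expected discordant counts are 33.0 and 23.7
- expected z ≈ (33.0 − 23.7)/√56.7 ≈ 1.24, so the chance of |z| > 1.96 is about 0.24

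Simulation (40,000 replicates, no continuity correction) gives 0.235 for this case. Simulated rejection rates with zero app effect, as the range over ρ = 0.2 to 0.6:

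| Secular change | n = 312 | n = 276 |
|---|---|---|
| 0 points | 5% | 5% |
| 2 points | 11–17% | 10–16% |
| 3 points | 19–33% | 18–30% |
| 5 points | 45–75% | 41–70% |

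The test holds its nominal level only if nothing else changes over the 8 months.

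**Step 3: adherence.** The Outcomes section places the visual-analogue score in the stepped wedge and follows it with routine records. The Limitations section and the abstract place adherence or clinical outcomes in the surveys. If it is recorded in every period, the rank-9 row applies and the effect can be estimated. If it is recorded only in the surveys, the rank-5 row applies and it cannot.

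**The case against.** McNemar appears once, in the abstract. The body's Quantitative Data Analysis section plans descriptive summaries of adoption and its predictors, and the power section concerns associations between predictors and adoption. The objectives speak of potential effects. The primary clinical outcome has a period-adjusted analysis of records. The false-positive rates rest on assumed drifts and correlations. The Results section shows baseline complete in three facilities while follow-up runs in the first, so survey dates may be staggered and the collinearity less than exact.

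Most of this is fair and limits the point. It does not rescue the sentence in the abstract, which states what the test is for. A pooled McNemar would use no information from staggered dates, and the second interview would still coincide with exposure.

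A reader might infer more than the documents support:

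- **That adherence is tested by McNemar.** Nothing says so. The score is a percentage with no stated cut-off, and it is listed with the stepped-wedge outcomes.
- **That adoption is tested by McNemar.** Nothing says so either. It is defined by activation within 60 days of introduction and is planned for descriptive and predictor analyses.
- **That the study hypothesis rests on the before-after comparison.** The Principal Findings section says "We hypothesize that there will be measurable improvements in HIV service outcomes, particularly ART adherence and clinic retention", but the same sentence goes on to make the comparison with unexposed periods of the stepped wedge. The abstract's conclusion also refers adherence to that design.

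**Conclusion.** The point holds in limited form and is of moderate severity. A McNemar result on the two survey waves measures any app effect plus everything else that changed, and should not be reported as an intervention effect. This follows from the survey timing and the rollout schedule and needs no numerical assumption beyond all four facilities having crossed over by the follow-up survey. The size of the error depends on drift that the article does not give. Under the assumptions shown, 2 to 5 points of drift turn a 5% error rate into roughly 11–75% at 312 men.

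The conflict over the source of visual-analogue adherence is real but unresolved. The article does not establish that the measure is survey-only. If it is, no stepped-wedge effect on it can be identified. The analysis of missed appointments is untouched.

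**What to change.** 1. In the abstract, remove McNemar as a test of intervention effects. Report paired survey changes as uncontrolled before-after changes with confidence intervals, and bring the abstract into line with the Quantitative Data Analysis section.
2. Keep effect claims for outcomes measured in every stepped-wedge period.
3. State where and when visual-analogue adherence is recorded, and reconcile the Outcomes section with the abstract and the Limitations section. If it is recorded at routine visits in every period, say so and keep it in the stepped-wedge model. If it is survey-only, report it as uncontrolled change and rest the stepped-wedge adherence claim in the abstract's conclusion and in Principal Findings on the medication possession ratio, already a listed secondary outcome.
4. Add the lack of a concurrent control in the pre-post component to the Limitations section.

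The cost is the loss of a nominal effect claim on two-wave survey outcomes. No new data are needed. Follow-up is expected to finish in August 2026, so the change can be made before analysis.

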**Results:**

This study received institutional review board approval in July 2025 and was registered on ClinicalTrials.gov in August 2025. Recruitment began in September 2025 and concluded in November 2025. A total of 307 men living with HIV were recruited across the 4 clinics for the pre- and postquantitative assessment. Preliminary findings will describe implementation outcomes and early effects on HIV care engagement.

**Conclusions:**

This trial will use a stepped-wedge design to evaluate the implementation and effects of the Nishauri mHealth intervention on antiretroviral therapy adherence and clinic attendance among men in Homa Bay County. By examining both clinical outcomes and the influence of masculine norms on intervention uptake, it will provide robust evidence on the effectiveness of mHealth strategies tailored for men in low-resource, high–HIV-burden settings. Findings will inform the design, scalability, and optimization of similar interventions by identifying key implementation barriers and facilitators.

## Introduction

Globally, men are 27% less likely than women to seek HIV testing and often present to care at later stages of illness [1]. In sub-Saharan Africa, men’s participation in HIV care is further constrained by cultural expectations that prioritize economic provision, requiring men to focus on work and income generation over health-seeking. Additionally, norms around emotional suppression discourage men from expressing vulnerability or seeking support, including attending health services [2,3]. Recent studies highlight that men who conform to traditional masculine norms are less likely to attend routine HIV care and more likely to disengage from treatment [4-6]. Despite advances in antiretroviral therapy (ART) and HIV care services, men experience persistent barriers to accessing and engaging with care. Masculine norms around strength, stoicism, and self-reliance often discourage men from seeking health services, including HIV testing and treatment [4], contributing to lower engagement and adherence [7,8]. The lack of men-targeted interventions compounds these challenges, making it critical to develop and evaluate strategies that effectively engage men in care to achieve the Joint United Nations Programme on HIV/AIDS 95-95-95 targets by 2030.

Mobile health (mHealth) interventions have emerged as promising tools for improving health care delivery and patient engagement, particularly in resource-constrained settings [8-10]. By leveraging mobile devices to deliver health-related information and services, mHealth strategies help bridge critical gaps in access, communication, and continuity of care. Evidence from low- and middle-income countries indicates that mHealth interventions, such as SMS reminders and mobile apps, can improve ART adherence, retention in care, and health literacy [4,7] among people living with HIV. Studies globally and in sub-Saharan Africa have shown the potential of mHealth interventions to enhance clinical outcomes, reduce loss to follow-up, and strengthen engagement in care [4,7,10-13]. For instance, studies in Uganda and South Africa show that mobile reminders and SMS-based counseling significantly improve adherence and retention among individuals with HIV [14-16]. These tools facilitate behavior change through personalized messaging, medication reminders, and educational content. Critically, culturally adapted mHealth interventions targeted for men are more effective, as they address stigma and align health-seeking behaviors with socially accepted masculine norms. For example, SMS reminders framed around men’s responsibilities or apps providing discreet, personalized health information have been shown to improve ART adherence and clinic attendance among men in sub-Saharan Africa [14-17]. This demonstrates how aligning messages and delivery with socially accepted masculine norms can reduce stigma and enhance engagement. However, there remains limited evidence on the implementation outcomes, service outcomes, and long-term sustainability of mHealth interventions specifically tailored for men in HIV care in Kenya, a country that continues to face significant challenges in the fight against HIV/AIDS, with an estimated 2.4% of the population being HIV-seropositive [18].

In Kenya, the Nishauri (client-centered mHealth digital) platform was developed to enhance HIV care management by supporting appointment reminders, ART adherence, patient-provider communication, and educational messaging. Pilot implementations of Nishauri and its predecessor, Ushauri, have shown promise in improving engagement and retention, though systematic evidence on its adoption and sustained use, particularly among men, remains limited [19,20]. While mHealth technologies such as Nishauri have shown promise in improving HIV care outcomes [21,22], their adoption and sustained use in Kenya remain at an early stage and face significant challenges. Structural barriers, including digital literacy gaps, inconsistent device ownership, limited infrastructure, and concerns around data privacy and confidentiality, continue to hinder equitable uptake [23,24]. Mobile phone ownership and digital access also vary by gender, education level, and socioeconomic status [25], with men in rural, high-prevalence settings like Homa Bay County often facing compounded disadvantages. Beyond structural issues, many mHealth interventions are not adequately aligned with the gendered and sociocultural realities that shape care-seeking behaviors. Programs often lack meaningful provider involvement and fail to tailor delivery to address male-specific barriers or local norms [26]. Although designed to be discreet and convenient, mHealth tools may fall short if they do not resonate with prevailing masculine identities or reframe care-seeking in ways that affirm strength and responsibility [17]. In high-burden regions such as Homa Bay, where HIV prevalence is 16.2% [18,27], men frequently disengage from care due to stigma and perceived threats to masculinity [28].

In parts of Homa Bay and other counties where Nishauri has been implemented on a pilot basis for over 6 months, its uptake and use remain low and highly variable across facilities, providers, and patient populations. This variability hints at challenges with its implementation and effectiveness among men, a population that faces unique sociocultural barriers to HIV care. Existing research often overlooks the role of gender norms and contextual factors in influencing men’s engagement with digital health interventions. Addressing this gap is essential for designing scalable, culturally relevant mHealth solutions that promote sustained engagement and improved clinical outcomes among men. This study will be guided by an integrated conceptual framework combining Connell’s theory of hegemonic masculinity [29] and the technology acceptance model (TAM) [30,31] to underpin the design and evaluation of Nishauri, predicting how individual factors (eg, perceived usefulness, usability, and masculinity norms) and system-level factors (eg, workflow integration and provider support) influence adoption, engagement, and sustainment of the intervention.

This study aims to assess the implementation and potential effects of the Nishauri mHealth intervention on HIV care and treatment outcomes among men aged 18‐55 years in Homa Bay County, Western Kenya. Specifically, it seeks to (1) analyze its potential effects on HIV care and treatment outcomes, (2) explore the role of masculine identity in modifying its acceptability and uptake, and (3) identify barriers and facilitators of its adoption, use, and sustainment.

